### Randomization

After signing written informed consent and completing baseline data collection, patients eligible for the trial in each trial site will be assigned randomized by investigators with 1:1 ratio to the simple random method, using a computer-generated random number sequence conducted by an independent statistician using SPSS (version 21.0). Sealed, opaque envelopes with printed randomization numbers on them are available in each center. According to the sequence of patients entering clinical observation, the corresponding random number was selected.

Following allocation, the subjects will receive corresponding treatment and be ensured continued supply for 12 weeks by a clinician in each site.

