### Sample size

The sample size will be calculated by PASS (version 15.0) and based on the effective rate of treatment. Group sample sizes of 91 in the treatment group and 91 in the control group achieve 90% power to detect a difference between the group proportions of 0.18. The proportion in the treatment group is assumed to be 0.91, and the proportion in the control group is 0.73 [18]. The significance level of the test is 0.025. With assuming attrition rate of 10%, a planned recruitment target of 200 patients will be set, 100 in each group.

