### Screening and recruitment of participants

This study intends to enroll 200 cases mainly from the nephrology outpatient and inpatient departments, including 80 cases from Shanghai Municipal Hospital of Traditional Chinese Medicine, 60 cases from the Sixth People’s Hospital affiliated to Shanghai Jiaotong University, and 60 cases from Baoshan Hospital of Integrative Chinese and Western Medicine Affiliated to Shanghai University of Traditional Chinese Medicine. According to the inclusion and exclusion criteria set based on diagnostic criteria for rUTI and TCM syndrome differentiation, rUTI patients diagnosed with the qi-yin of spleen and kidney deficiency, damp-heat adhesion syndrome by TCM, will be considered as potential participants.

We have taken several methods to ensure recruiting enough participants to reach the target sample size. These methods are shown as follows:
We have counted the outpatient visits of the Nephrology Departments (sub-centers) of these three hospitals over the past three years in advance. And the statistical results showed that the annual outpatient visits of each Nephrology Department in each hospital exceed 60,000 per year. Therefore, each sub-center has enough rUTI patients to support the progress of this study.In order to recruit enough suitable subjects in time, we put recruitment advertisements in all three sub-centers.In order to avoid case shedding during observation and follow-up, we have special investigators responsible for contacting the subjects regularly and reminding and helping them to complete the detection and follow-up on time.

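### Simple, unstratified randomisation over three centres does not secure the planned 100:100 split or balance within centres; centre-stratified blocks would be a cheap, minor improvement

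*Protocol article*

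**What the plan says.** The Randomization section states that eligible patients at each site "will be assigned randomized by investigators with 1:1 ratio to the simple random method". The sequence is computer-generated by an independent statistician. For its delivery, "Sealed, opaque envelopes with printed randomization numbers on them are available in each center", and numbers are taken in the order in which patients enter. The section mentions no block size and no stratification factor.

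The Sample size section requires 91 per group and, after an allowance for attrition, "a planned recruitment target of 200 patients will be set, 100 in each group". The section on screening and recruitment says "This study intends to enroll 200 cases mainly from the nephrology outpatient and inpatient departments" and divides them by hospital, "including 80 cases from Shanghai Municipal Hospital of Traditional Chinese Medicine" and 60 from each of the other two. The Blinding section says that the placebo and the active granules have matching packages.

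**The concern.** The article does not leave the allocation method open. It names one, and that method fixes neither the total per arm nor the split within a hospital. Yet the same article plans equal groups of 100 and sets a recruitment target for each centre.

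The centres are a municipal hospital of traditional Chinese medicine, a general university-affiliated hospital and an integrative hospital. Patients come from both outpatient and inpatient departments, and eligibility depends partly on a syndrome diagnosis that includes tongue and pulse findings. Different recurrence risks between centres are therefore plausible, although nothing in the article documents them. If they exist, a chance excess of one arm in a higher-risk centre moves the unadjusted treatment difference. Stratified allocation would prevent nearly all of that at little cost.

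**Working it through.** **Inputs from the article.** Total 200, with 100 per group; 91 per group required; assumed rates 0.91 and 0.73 (difference 0.18); 90% power; significance level 0.025; attrition 10% (Sample size). Centre targets 80, 60 and 60 (Screening and recruitment). Simple 1:1 allocation (Randomization). Two-sided tests at 0.05 (Data analysis).

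**1. The plan's own figure.** Two-proportion formula with unpooled variance, reading 0.025 as one-sided (two-sided 0.05):
n = (1.960 + 1.282)² × (0.91×0.09 + 0.73×0.27) / 0.18² = 90.48, rounded up to 91 per group. This matches. For attrition, 182 / 0.9 = 202.2, against 200 planned, which is close enough for the present purpose.

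**2. Overall split.** Under simple randomisation the number in one arm is Binomial(200, 0.5).
- P(exactly 100:100) = 5.6%, about 1 trial in 18.
- P(90:110 or worse) = 17.9%. This is also the chance that one arm randomises fewer than 91.
- The central 95% range for one arm is 86 to 114.

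**3. Split within centres.** Binomial(80, 0.5) and Binomial(60, 0.5), independent between centres.
- Centre of 80: P(45:35 or worse) = 31.4%. The 95% range for one arm is 31 to 49.
- Each centre of 60: P(35:25 or worse) = 24.5%. The 95% range for one arm is 22 to 38.
- At least one centre differing by 10 or more: 1 − (1 − 0.314) × (1 − 0.245)² = 0.61.

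**4. Effect on power.** Pooled two-proportion test, two-sided 0.05, rates 0.91 and 0.73, all 200 analysed.
- 91.8% at 100:100, and 91.7% averaged over the splits that simple randomisation produces: a loss of about 0.1 point.
- At 114:86, the edge of the 95% range, power is 91.1% to 91.6%, depending on which arm is larger.
- Relative information at 90:110 is 4 × 90 × 110 / 200² = 0.99, a loss of 1%.
- For an analysis stratified by centre, expected information is the sum of (n − 1)/4 = (79 + 59 + 59)/4 = 49.25, against 50 with perfect balance: a loss of 1.5%.

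**5. Shift from imbalance by centre.** Suppose, as an assumption, that recurrence in the 80-patient centre differs from that in the other two by g points. The shift in the unadjusted difference is g × (share of that centre in one arm − its share in the other). The standard deviation of the difference in shares is about √(0.4 × 0.6 × (1/100 + 1/100)) = 0.069, and 1.96 × 0.069 = 0.136.

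| Assumed gap g (points) | Shift exceeded in 5% of trials (points) |
|---|---|
| 10 | 1.4 |
| 20 | 2.7 |
| 30 | 4.1 |

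With g = 20, a shift of 2 points or more occurs in about 16% of trials (exact binomial calculation). The yardstick is the planned difference of 18 points.

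**6. After the change.** With blocks of 4 by centre as an illustration, 80 and 60 are both divisible by 4. Full targets then give 40:40, 30:30 and 30:30, hence 100:100, and the arms in a centre never differ by more than 2 at any time. With blocks of varying size the last block in a centre may be incomplete, so the balance is close but not guaranteed to be exact. The sample size does not change.

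**The case against.** The case against is largely right about the size of the harm. Simple randomisation is unbiased, and the error rate of the test already covers chance imbalance. The cut-off of 10 patients is arbitrary; the 61% counts how often arms differ, not what that does to the result. No section reports centre differences, and much of the plan favours uniformity: three nephrology departments, common eligibility criteria, one regimen and a central laboratory. All of this stands, and it makes the point minor.

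The figure of 100 per group is also a planning target, and quoting the expected split of a 1:1 design is ordinary. A reader might infer that the article contradicts itself or claims a split that it cannot have. The text does not support that; it only fails to secure the target.

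The list might have been forced to equal totals. The article does not say so, and the method would then not be simple randomisation. The total would balance if all 200 enrol, but imbalance within centres would remain, with a standard deviation of about 3.5 patients in the centre of 80 and 3.2 in each centre of 60.

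Finally, adjustment for centre is normally specified in the statistical analysis plan, which is not shown. Its absence here is not a fault and is not claimed as one.

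**Conclusion.** The point holds as a minor design weakness. The stated method secures neither the planned group sizes nor balance within centres, and the probabilities in steps 2 and 3 follow directly if it is applied as written.

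Two stronger readings fail. One is that the treatment comparison is confounded by centre: allocation does not depend on prognosis, so what arises is extra random variation, not systematic bias. The other is that the 18% chance of fewer than 91 in one arm leaves the trial underpowered: power depends on both arms together and hardly moves.

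What remains is avoidable noise. Its size rests wholly on an assumed gap between centres. Over assumed gaps of 10 to 30 points, the shift exceeded in 5% of trials stays well below the planned effect. If the centres do not differ, there is no shift at all.

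**What to change.** In the Randomization section, replace simple randomisation with permuted blocks of varying size, stratified by centre, with block sizes not disclosed to the sites. Include centre as a factor in the primary analysis, for example through a Mantel-Haenszel risk difference.

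The cost is small but not zero. The same statistician can produce the lists, and envelopes are already held in each centre, though they would have to be reissued. Blocks bring some predictability; the matching placebo and varying sizes limit it but do not abolish it. Recruitment was due to begin in August 2021 (Trial status). If it has begun, the change is a protocol modification that needs the agreement and ethics approval described under Ethics approval, and the report would have to describe two allocation schemes.

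If the list cannot be changed, keep it and adjust the primary analysis for centre, fixed before unblinding. That removes the shift due to centre for a loss of about 1.5% of information, recovers most of the benefit, and does not affect recruitment. If the existing list was in fact balanced or blocked, correct the description instead.

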### Blinding

This trial follows the double-blind design. The division of the groups in this study will be blinded to all participants, investigators, and statisticians. The placebo and TLF are the same in the appearance of the drug package. What’s more, the drug distribution will be conducted by a pharmacist who is not involved in the study.

To assess whether participants stayed masked or knew their assignment, we will use the direct questioning method at the end of follow-up, that is, design a question in the CRF to ask the subjects to guess which group they are assigned to and ask them to give the basis or reason of guess. Then calculate blinding index (BI) according to the guess result and the implementation of the blind method can be judged.

### Intervention

Patients who are diagnosed with non-acute uncomplicated rUTI or were in remission after 14 days of treatment with sensitive antibiotics during acute episodes will be enrolled after signing informed consent. Then they will be randomly assigned to the treatment group or the control group.

### Treatment group

Participants randomly assigned to the treatment group will be administered TLF combined with CLAT.

#### Dosage and duration (Table 1)

TLF: one package as an oral dose four times daily (15 min after three meals and 1 h before bedtime) for 12 weeks;

**Table 1 Tab1:** Interventions: administration methods and duration in the experimental and control group

Treatment	Time					
	Week 0–2	Week 3–4	Week 5–6	Week 7–8	Week 9–10	Week 11–12
**TLF**	**○**	**○**	**○**	**○**	**○**	**○**
**Placebo**	**●**	**●**	**●**	**●**	**●**	**●**
**CLAT**						
**Levofloxacin** (0.1 g, QN, po)	**○●**			**○●**		
**Nitrofurantoin** (0.1 g, QN, po)		**○●**			**○●**	
**Cefdinir** (0.1 g, QN, po)			**○●**			**○●**

A white circle represents the treatment of the treatment group; a black circle represents the treatment of the control group

CLAT: first, levofloxacin 0.1 g taken orally once per night for 2 weeks; next, nitrofurantoin 0.1 g taken orally once per night for 2 weeks; then, cefdinir 0.1 g taken orally once per night for 2 weeks. And then repeat one turn in accordance with the medication order above, the total course of antimicrobial therapy is 12 weeks. All antibiotics are taken 15 min after dinner. For those allergic to any of the three antibiotics, trimethoprim-sulfamethoxazole (TMP 40 mg, SMZ 200 mg) one tablet per day orally or fosfomycin-trometamol (3 g, qod, po) will be used as the alternative drug.

### Control group

Participants randomly assigned to the control group will receive placebo plus CLAT the dosage and administration of which are the same as the treatment group (Table 1).

We will conduct health education for all groups. And the method of drug administration will be instructed to all co-investigators and patients. The TLF granules will be manufactured by Jiangyin Tianjiang Pharmaceutical Co. LTD.

#### Treatment of acute-onset UTI during the treatment period

Conduct urine culture, antimicrobial susceptibility testing, and the colony count immediately, then give a sufficient amount of oral or parenteral antibiotics for 7–14 days. Acute-onset infections should be treated with culture-directed antibiotics according to patients’ existing antimicrobial susceptibility testing records at first. In other situations, antibiotics will be prescribed empirically while awaiting the result of urine culture.

Such cases mentioned above should be marked as no recovery (NR).

#### Concomitant medications

Non-antibiotic drugs or products that may affect efficacy judgments are specifically prohibited during this trial, including cranberries, lactobacillus, D-mannose, methenamine, and other herbs. Any drugs other than those used to treat rUTI must be recorded on the observation sheet, including drug name, dose, and treatment duration.

### Items to be measured and the time points of data collection

Patient data, efficacy-related examinations, and indicators will be performed and collected at 2 weeks before baseline, baseline, and every 2 weeks or 4 weeks during treatment and follow-up period.

Measurement items and the time points of data collection are listed in Table 2.

**Table 2 Tab2:**
[figure not shown]
SPIRIT figure: Items to be measured and time points of data collection

*HCG* human chorionic gonadotropin, *TCM* traditional Chinese medicine, *Urine NAG/Cr* urine glucosaminidase/creatinine, *β2-MG* β2-microglobulin, *α1-MG* α1-microglobulin, *UTFR* urinary transferrin, *PTX 3* pentraxin 3, *Scr* serum creatinine, *BUN* blood urea nitrogen, *GOT* glutamic oxalacetic transaminase, *GPT* glutamic-pyruvic transaminase

Blood and urine samples will be collected at each site and transported to the central laboratory for unified measurement, analysis, and eventual destruction. No additional collection of samples will be obtained for storage or future testing during the conduct of this trial. All samples will be coded with their unique identifier and logged in the electronic data systems (EDS). The researchers who will carry out analyses on these samples will not have access to any information of subjects or intervention.

The following methods should be used to minimize attrition and reduce potential loss to follow-up in this clinical trial.
Detailed introduction for patients including the whole process of the clinical study and its requirements and possible risksSpecial investigators will be responsible for contacting the subjects by telephone regularly and helping subjects receive treatment and testing on time

## Outcomes

### Primary efficacy outcome

The primary efficacy outcome will be the recurrence rate at the 12th week of the follow-up period.

### Secondary efficacy outcomes

The secondary efficacy outcomes will be the post-treatment changes in renal and liver function, including serum creatinine (Scr), blood urea nitrogen (BUN), glutamic oxalacetic transaminase (GOT), and glutamic-pyruvic transaminase (GPT). Furthermore, TCM symptoms, non-infection-related physical signs, and subjective symptoms will be scored, and the number of episodes of each subject will be recorded. Meanwhile, vital signs indicators and SAEs will be monitored throughout the trial.

### Safety indicators

Incidence of SAEsVital signs indicators (electrocardiogram, blood routine, urine routine, fecal routine and occult blood test, liver and renal function test)

## Therapeutic effect evaluation

### TCM syndrome scores

According to the *Guidelines for Clinical Research of Chinese Medicine (New Drug)* [21], the primary symptoms of the qi-yin of spleen and kidney deficiency and damp-heat adhesion syndrome will be scored 2, 4, and 8, while secondary symptoms will be scored 1, 2, and 4. The scores will be added for each patient, separately. The evaluation was conducted once before treatment and the 12th week after.

The two total scores calculated by the measurement scale for TCM symptoms before treatment and the 12th week after for each patient will be added together, and then used to calculate an efficacy indicator (EI) for the evaluation of treatment efficacy:

EI = (Total symptom score at baseline − Total symptom score post-treatment)/Total symptom score at baseline × 100%

Symptom improvement degree will be presented in four levels showed in Table 3.

**Table 3 Tab3:** The degree of symptom improvement

Degree	Indicators			
	EI	Clinical symptoms and signs	Urine routine (for two consecutive times)	Clean-catch midstream urine culture
Full recovery (FR)	≥ 95%	Disappeared	Normal	Negative
Good recovery (GR)	<95% ≥70%	Disappeared or nearly disappeared	Normal or almost normal	Negative
Modest recovery (MR)	<70% ≥30%	Alleviated	Significantly improved	Occasionally positive
No recovery (NR)	<30%	No significant improvement	No significant improvement	Colony count ≥10^5^/ml 4 weeks after medication

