### Short-term and long-term cure rate

It will be recorded as a short-term cure if present of *full recovery* (FR) 4 weeks after the end of the medication and be recorded as a long-term cure if present of FR 12 weeks after the end of the medication [21] (Table 3).

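### Short-term and long-term cure need a symptom score at weeks 16 and 24, but the text provides one post-baseline score with no stated anchor

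*Protocol article*

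**What the plan says.** The section on TCM syndrome scores fixes when symptoms are scored: "The evaluation was conducted once before treatment and the 12th week after". It then speaks of two totals per patient, "The two total scores calculated by the measurement scale for TCM symptoms before treatment and the 12th week after for each patient", and defines the indicator as "EI = (Total symptom score at baseline − Total symptom score post-treatment)/Total symptom score at baseline × 100" per cent.

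Table 3 grades response in four rows using EI, clinical symptoms and signs, urine routine and urine culture. The top row reads "Full recovery (FR) ≥ 95% Disappeared Normal Negative". The culture entry of the no-recovery row has its own timing, "4 weeks after medication".

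The section on short-term and long-term cure rate applies the top row at two dates. It records a "short-term cure if present of *full recovery* (FR) 4 weeks after the end of the medication", and a long-term cure on the same criterion at 12 weeks, with a reference to Table 3.

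The Intervention section enrols patients with non-acute disease or those who "were in remission after 14 days of treatment with sensitive antibiotics during acute episodes", and new-onset acute infection is an exclusion criterion.

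**The concern.** Two full-recovery assessments after medication are defined, but only one symptom total after baseline is described. One total cannot serve two dates. Because EI is part of full recovery, a cure rate without a score from its own date is either missing or filled with a score from another date. Under one reading that other date is the last week of treatment, when the patient is still on drug and has had no chance to recur off treatment. A cure rate built that way would not measure what its name says, and a later analysis plan cannot recover a score that was never collected.

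There is also a smaller problem in Table 3. Patients enter without acute infection, yet the two lower rows describe urine findings that presuppose bacteriuria. With no rule for columns that disagree, such patients would be graded by judgement.

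**Working it through.** The article gives no figure for the cure rates, so there is none to reproduce. The check sets required dates against available dates and then runs through the table.

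**Dates**

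- Medication lasts 12 weeks and follow-up another 12 (Trial design; Dosage and duration).
- Short-term cure: 12 + 4 = week 16.
- Long-term cure: 12 + 12 = week 24.
- Post-baseline TCM score: one, at a 12th week that is counted either from the start of treatment (week 12) or from the end of medication (12 + 12 = week 24).

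| Reading of the 12th week | Score at | EI for short-term cure (week 16) | EI for long-term cure (week 24) |
|---|---|---|---|
| From start of treatment | week 12 | none | none |
| From end of medication | week 24 | none | available |

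Short-term cure has no EI under either reading. Long-term cure has one only under the second.

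Table 3 also mixes dates within a row. The no-recovery culture falls at week 4 or week 16, depending on whether it is counted from the start or the end of medication, and the EI falls at week 12 or week 24. No pairing coincides.

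**Is EI defined for patients who enter in remission?**

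- Entry requires two primary symptoms, or at least one primary and more than two secondary (TCM syndrome differentiation).
- Primary symptoms score 2, 4 or 8; secondary symptoms score 1, 2 or 4.
- Lowest eligible total: two mild primary symptoms, 2 + 2 = 4. One mild primary with three mild secondary gives 2 + 3 = 5.
- Highest total: 2 × 8 + 4 × 4 = 32.

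The baseline total is therefore never zero, and EI can always be calculated once a later score exists.

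**Which rows can a patient with normal urine and negative culture throughout match?** Taking a baseline total of 8 as an illustration:

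- Later total 0: EI = 8/8 = 100%. With symptoms gone, the full-recovery row matches.
- Later total 2: EI = 6/8 = 75%. With symptoms nearly gone, the good-recovery row matches.
- Later total 4: EI = 4/8 = 50%. This is in the modest-recovery band, but that row expects an occasionally positive culture and clearly improved urine. No full match.
- Later total 6: EI = 2/8 = 25%. This is in the no-recovery band, but that row expects a colony count of at least 10^5/ml. No full match.

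The table fails for these patients below an EI of 70% and works above it. In both failing cases the patient is plainly not in full recovery, so the cure classification is unaffected.

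**The case against.** The strongest reply is that the data may be there. The section on items to be measured says that examinations and indicators are collected every 2 or 4 weeks during treatment and follow-up, and it refers to Table 2, which is not shown. Score visits at weeks 16 and 24 cannot be ruled out. This stands as far as it goes: it cannot be claimed that the scores will certainly be absent. But the section on TCM scores states specifically that there are two totals per patient. Extra scores in Table 2 would contradict that statement, and a general sentence on visit frequency does not settle it.

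A second reply is that tie-break rules are commonly left to a full protocol or analysis plan, and that the section on acute-onset UTI already assigns no recovery to acute infections during treatment. This has weight for the table and is why that part is secondary. The existing rule covers only infections in the treatment period and does not help a patient whose urine was clean throughout.

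A reader might infer that Table 3 cannot classify patients who enter in remission at all. The documents do not support that: TCM symptoms are required at entry, and the two upper rows can be reached. A reader might also infer that a single residual sign blocks cure because of the EI threshold when the baseline total is low. The threshold is not what decides this, since the full-recovery row separately requires symptoms to have disappeared, whatever the baseline.

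**Conclusion.** The timing point holds. As the text stands, the short-term cure rate has no EI under either reading of the 12th week, and the long-term cure rate has none if the week is counted from the start of treatment. This assumes that all four entries of the full-recovery row are required and that the section on TCM scores, not the unseen Table 2, governs when scores are taken.

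The consequence is limited. The cure rates are not named among the primary or secondary outcomes. The primary outcome is recurrence, and the section on relapse or reinfection describes an episode by symptoms and culture, using neither EI nor Table 3. It is tempting to link the grading to the effective rate behind the sample size, but the article does not define that rate, so the link would be conjecture; nothing here changes the sample size.

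The gap in the modest- and no-recovery rows is real but secondary. It affects the four-level grading, not full recovery versus anything less. The correction should be made, because it is cheap and a stated outcome cannot otherwise be computed from data of its own date.

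**What to change.** In the section on TCM syndrome scores:

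- State the study week of each score, counted from a named starting point.
- Add scores at week 16 and week 24.
- State that EI for short-term cure uses the week 16 score and EI for long-term cure uses the week 24 score, each against baseline.
- Bring Table 2 into line with this.

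Under Table 3, add a rule for columns that disagree, including how the urine columns are read when urine is normal and culture negative from entry onward. The rule should use only data from the same assessment time, so that a later episode cannot overturn an earlier grade, and should agree with the no-recovery rule in the section on acute-onset UTI.

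The cost is a short symptom score at two follow-up time points and one paragraph of text.

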#### TCM syndrome differentiation

rUTI Patients will be diagnosed with the qi-yin of spleen and kidney deficiency and damp-heat adhesion syndrome by TCM if they have at least one primary symptom and more than two secondary symptoms or two primary symptoms listed below [20].

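### TCM symptom efficacy is measured by banded percent change (EI), so the same week-12 score falls in different bands by baseline; a baseline-adjusted comparison of the score already collected would be better, and the sentence introducing EI contradicts its formula

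*Protocol article*

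**What the plan says.** Under Secondary efficacy outcomes, the article states that "TCM symptoms, non-infection-related physical signs, and subjective symptoms will be scored". The section on TCM syndrome scores gives the detail:

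- **Item scores.** Primary symptoms "will be scored 2, 4, and 8, while secondary symptoms will be scored 1, 2, and 4".
- **Timing.** "The evaluation was conducted once before treatment and the 12th week after".
- **Derived measure.** The two totals for each patient "will be added together, and then used to calculate an efficacy indicator (EI) for the evaluation of treatment efficacy".
- **Formula.** "EI = (Total symptom score at baseline − Total symptom score post-treatment)/Total symptom score at baseline × 100" (in percent).
- **Presentation.** "Symptom improvement degree will be presented in four levels showed in Table 3". The EI cuts are: full recovery (FR) at 95% or more, good recovery (GR) from 70% to below 95%, modest recovery (MR) from 30% to below 70%, and no recovery (NR) below 30%. Table 3 also lists, for each grade, a symptom indicator, a urine routine indicator and a urine culture indicator.

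Two other sections use the grades. Acute-onset infection during treatment is marked NR, and both cure rates (short-term and long-term) are defined by FR. The Data analysis section gives software, two-sided testing at 0.05 and missing-data handling, but no test for the TCM score, for EI or for the grades.

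**The concern.** Two things are wrong in what the article fixes.

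First, the sentence and the formula describe different operations. Summing items within a patient is already covered by an earlier sentence in the same section, so the later sentence cannot be read as meaning that.

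Second, EI is a ratio to baseline that is then cut into bands. A given week-12 symptom score has no fixed band; its band depends on where the patient started. Cutting also throws away differences within a band. Treatment allocation is by simple randomisation, so baseline severity may differ between arms by chance, and an unadjusted comparison of bands has no direct means of allowing for that. At stake are the precision and interpretability of one secondary efficacy result. The 95% cut is also one of the FR indicators, and so enters the two cure rates.

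**Working it through.** **1. The plan's own figure.** The article gives no sample size or power for the TCM score or EI. Its only calculation concerns the effective rate, 0.91 against 0.73. It reproduces with an unpooled two-proportion formula at one-sided 0.025 (two-sided 0.05) and 90% power:

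n = (1.960 + 1.282)² × [0.91×0.09 + 0.73×0.27] / 0.18² = 90.48, rounded up to 91 per group.

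I use 91 only as the arm size below.

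**2. Range of the baseline score (assumption).** I take the scale to be the two primary and four secondary entries listed for the syndrome, with 0 for an absent symptom. Eligibility requires "at least one primary symptom and more than two secondary symptoms or two primary symptoms listed below".

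- Minimum: two primary symptoms at 2 points = 4. (One primary plus three secondary = 2 + 3 = 5.)
- Maximum: 2×8 + 4×4 = 32.
- Eligible profiles: both primary present, 3×3×4⁴ = 9×256 = 2,304; exactly one primary with at least three secondary, 6×(4×27 + 81) = 6×189 = 1,134. Total 3,438.

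**3. EI band by baseline.** A final score R from baseline B reaches cut c when (B − R)/B ≥ c, that is, when B ≥ R/(1 − c). For R = 4:

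- 30% cut: B ≥ 4/0.70 = 5.7, so 6 or more.
- 70% cut: B ≥ 4/0.30 = 13.3, so 14 or more.
- 95% cut: B ≥ 4/0.05 = 80, which is out of range.

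For R = 1, the 95% cut needs B ≥ 1/0.05 = 20. From 20, EI = 95.0%; from 19, EI = 94.7%.

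Baselines that put a final score in each EI band (baseline at least as high as the final score):

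| Final score | NR band | MR band | GR band | FR band |
|---|---|---|---|---|
| 1 | – | – | 4–19 | 20–32 |
| 2 | – | 4–6 | 7–32 | – |
| 4 | 4–5 | 6–13 | 14–32 | – |
| 6 | 6–8 | 9–19 | 20–32 | – |
| 8 | 8–11 | 12–26 | 27–32 | – |
| 9 | 9–12 | 13–29 | 30–32 | – |

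Every final score from 3 to 9 spans three bands. The relation B ≥ R/(1 − c) holds for any scale; only the particular thresholds depend on the assumption in step 2.

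**4. Power (simulation, assumed effects).** 91 per arm, two-sided 0.05. All models use the EI bands alone.

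- Item-level model: latent severity cut into four levels per item, eligibility rule applied, treatment effect 0.45 latent SD, common improvement 1.0 (moderate) or 1.8 (larger) latent SD, 3,000 trials per scenario. The standard error of each estimate is at most √(0.25/3000) = 0.009.
- Additive model: baseline mean 15, SD 5; final mean 7, SD 4.5; effect 1.8 points.
- Proportional model: final score as a fraction of baseline, mean 0.47, lowered by 0.12 on treatment.

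| Model, correlation | ANCOVA | Rank ANCOVA | Mann–Whitney on bands | Chi-square on bands | MR or better | FR only |
|---|---|---|---|---|---|---|
| Item, moderate, 0.4 | 0.757 | 0.780 | 0.736 | 0.558 | 0.45 | 0.47 |
| Item, moderate, 0.7 | 0.855 | 0.868 | 0.839 | 0.689 | 0.57 | 0.51 |
| Item, moderate, 0.9 | 0.952 | 0.961 | 0.938 | 0.843 | 0.71 | 0.52 |
| Item, larger, 0.4 | 0.644 | 0.681 | 0.664 | 0.509 | not run | not run |
| Item, larger, 0.7 | 0.760 | 0.802 | 0.754 | 0.610 | not run | not run |
| Item, larger, 0.9 | 0.862 | 0.902 | 0.840 | 0.709 | not run | not run |
| Additive, 0.3 | 0.796 | not run | 0.713 | 0.554 | 0.409 | 0.387 |
| Additive, 0.5 | 0.863 | not run | 0.782 | 0.632 | 0.469 | 0.380 |
| Additive, 0.7 | 0.953 | not run | 0.840 | 0.687 | 0.535 | 0.349 |
| Proportional | 0.714 | not run | 0.693 | 0.540 | 0.442 | 0.369 |

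- ANCOVA minus chi-square: from 0.952 − 0.843 = 0.109 to 0.953 − 0.687 = 0.266, so about 11 to 27 points.
- ANCOVA minus Mann–Whitney: from 0.644 − 0.664 = −0.020 to 0.953 − 0.840 = 0.113, so −2 to +11 points.
- Rank ANCOVA minus Mann–Whitney: from 0.681 − 0.664 = 0.017 to 0.902 − 0.840 = 0.062, so about 2 to 6 points.
- Wherever a dichotomy was run, its power was below chi-square.

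With no treatment effect, rejection rates in the item-level model were 0.04 to 0.06 for the four methods tested (both ANCOVAs, Mann–Whitney and chi-square).

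**The case against.** **No test is fixed.** The article says the levels will be presented; it does not say the arms will be compared by chi-square or by a cut of the grades, nor that the raw score will go unanalysed. An analysis plan that is not shown may supply a model. This stands: the absence of ANCOVA is not itself a finding, and a reader should not infer that the plan commits to the weakest test. What the article does fix is EI as the efficacy measure, and that can be criticised as it stands.

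**The power gain depends on the comparator.** This also stands. It is tempting to say that ANCOVA always wins. It does not: with larger improvement and correlation 0.4 it falls slightly below the ordinal test (0.644 against 0.664), and under a proportional effect a t-test on continuous EI did about as well (0.750 against 0.714). Rank-based adjustment stayed ahead in every item-level scenario.

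**Table 3 is more than EI.** A final score of 9 from 32 gives EI = 23/32 = 71.9%, inside the GR band, while the GR symptom entry reads "Disappeared or nearly disappeared". A reader might infer that the grades contradict their own clinical description. The article does not support that. The symptom entry is a separate indicator beside urine routine and culture, and nothing says EI alone assigns the grade. The arithmetic above applies to the EI column only, and the simulations do not model the full grades.

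**The scale is not reproduced.** It may score dysuria, frequency and urgency separately, so the exact thresholds are illustrative.

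**The sentence is harmless in practice.** Largely true: the formula is explicit, so the correction is editorial.

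**Conclusion.** The point holds in a limited form. EI and its bands, as fixed in the article, do not place week-12 symptom scores on a common footing; this follows from the formula and needs no simulation. The quoted thresholds (three possible bands for a final score of 4, and a baseline of 20 for a residual of 1) assume six items with 0 for absent.

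How much power the banding costs is uncertain because it turns on a test the article does not state. Under the assumed effects the cost is substantial for chi-square or a dichotomy and small for an ordinal test. The contradiction between sentence and formula is certain but has no numerical effect if the formula is followed.

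This concerns a secondary outcome. It does not touch the primary recurrence comparison or the stated sample size. The change is worth making because it needs no new data.

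**What to change.** 1. State that the between-arm TCM symptom result is the week-12 total score compared by ANCOVA, with baseline score and centre as covariates, reported as an adjusted mean difference with 95% CI. Name a rank-based ANCOVA as a check, or as the alternative if scores pile up at zero.
2. Report the EI bands as a supportive summary of TCM symptoms. Leave the Table 3 grades in place where other sections rely on them (NR for acute-onset infection during treatment, FR for the two cure rates). Making Table 3 purely descriptive would break those definitions.
3. In the sentence introducing EI, drop the instruction to sum the two totals, so that it says only that both are used to calculate EI by the printed formula.

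Cost: wording in the therapeutic-effect and analysis sections and one more model. Both scores are already collected, so no visits or patients are added. The downside is a headline less familiar to readers used to the guideline-based grades.
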